## Glossary of abbreviations and terms

| Abbreviation or term                                 | Description                                                                                                                                                                                                                                                                                                                             |
|------------------------------------------------------|-----------------------------------------------------------------------------------------------------------------------------------------------------------------------------------------------------------------------------------------------------------------------------------------------------------------------------------------|
| Antibiotic-associated adverse event                  | Any unexpected adverse reaction to a prescribed antibiotic (e.g. allergic reaction, end-organ toxic effect, gastrointestinal intolerance, haematological abnormalities, etc)                                                                                                                                                            |
| Clostridioides difficile associated diarrhoea | Diarrhoea (with or without colitis) demonstrated to be caused by infection from the bacterium Clostridioides difficile , generally associated with recent antibiotic use                                                                                                                                                         |
| Diabetic foot infection                              | Soft tissue and/or bone infection of the foot in the setting of diabetes and associated neuropathy and/or peripheral arterial disease                                                                                                                                                                                                   |
| Immunosuppression                                    | Medical condition or iatrogenic cause resulting in reduction of immune response (e.g. solid organ tumour, transplant recipient, human immunodeficiency virus infection, splenectomy/functional asplenia, immunosuppressing medications)                                                                                                 |

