### 2.3 Outcomes

#### **Primary Outcome measures**

The primary endpoint will be feasibility and safety of the trial.

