#### Safety outcomes

- SAEs, including all-cause mortality
- Antibiotic-associated adverse event
- Clostridioides difficile* associated diarrhoea
- Number of hospital readmissions during the follow-up period related to treatment of diabetic foot infection or complications arising

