**Figure 1: Study design overview**

### 3.6 Antibiotic choice

Antibiotic choice, including agent, dosing and route of administration, will be at the discretion of treating clinicians based on the results of any relevant microbiological culture and susceptibility results, such as wound swab cultures.

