### 3.9 Follow up assessment data

Follow up will be at Day 14 ( $\pm$  2 days), day 42 ( $\pm$  2 days) and day 90 ( $\pm$  5 days) from date of recruitment. Data collected at these assessments will include:

- Attendance at follow up
- Mode of follow up assessment (i.e. in-person, telehealth (video) or telephone consult)
- Medication-related adverse events (see Appendix 3)
- Medication adherence assessment (see Appendix 4)
- Ulcer size
- Wlfl score
- Serum biomarkers (total peripheral white cell count, serum C-reactive protein)
- Changes to antibiotic therapy

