### Appendix 3 – Medication adverse event assessment

| Adverse event category  | Adverse event and definition                                                                                                                                                                                                                                                             | Present at review (Yes/No) | Details |
|-------------------------|------------------------------------------------------------------------------------------------------------------------------------------------------------------------------------------------------------------------------------------------------------------------------------------|----------------------------|---------|
| Gastrointestinal | Diarrhoea: >3 loose stools per day associated with antibiotic administration in the absence of laxative or pre-existing enteritis                                                                                                                                                        |                            |         |
|                         | Nausea and vomiting: associated with antibiotic administration, in the absence of alternate explanation                                                                                                                                                                                  |                            |         |
| Haematologic     | Anaemia: Hb<100g/L                                                                                                                                                                                                                                                                       |                            |         |
|                         | Leukopenia: WCC < 4.0 x 10  /L                                                                                                                                                                                                                                               |                            |         |

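### The adverse event checklist (Appendix 3) is narrower than the open-ended outcome it feeds and has no row for other reactions, so unlisted non-serious reactions may go unrecorded

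*Protocol*

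**What the plan says.** - **Status of the outcome.** Section 2.3 states "The primary endpoint will be feasibility and safety of the trial" and lists "Antibiotic-associated adverse event" among four safety outcomes. Section 6.2 reports safety outcomes as a risk difference with a 95% confidence interval.
- **Definition.** The glossary defines the event as "Any unexpected adverse reaction to a prescribed antibiotic", illustrated by an unfinished list: "e.g. allergic reaction, end-organ toxic effect, gastrointestinal intolerance, haematological abnormalities, etc".
- **Instrument.** At days 14, 42 and 90, section 3.9 collects "Medication-related adverse events (see Appendix 3"). No other form is named for non-serious reactions.
- **Content of the form.** Appendix 3 gives named events by organ system, each with a column "Present at review (Yes/No") and a details column. The last category is anaphylaxis. The gastrointestinal block holds diarrhoea and one joint row: "Nausea and vomiting: associated with antibiotic administration, in the absence of alternate explanation".
- **Range of treatment.** Under section 3.6 the antibiotic choice, "including agent, dosing and route of administration, will be at the discretion of treating clinicians".
- **Contrast.** Appendix 4, the adherence questionnaire, does offer a free-text option for other answers, in two of its questions.

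**The concern.** The definition and the form do not cover the same ground. The definition reaches any unexpected reaction and is left open by its examples, whereas the form can record only what it already names. A closed list suits an outcome defined by unexpectedness poorly, and it suits it less well when any agent and any route may be used, because the possible reactions cannot be fixed in advance.

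Gastrointestinal intolerance, which the glossary names in general terms, is reduced to two rows. The joint nausea and vomiting row can be scored in two ways, so sites may differ.

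At stake is the recorded rate of a safety outcome within the primary endpoint. Section 6.1 intends the trial to supply estimates for the power calculation of later trials. No analysis plan can recover a reaction that the form never collected.

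**Working it through.** **1. Is there another route for a non-serious, unlisted reaction?**

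| Place in the protocol | What it captures | Does it record the unlisted reaction? |
|---|---|---|
| Appendix 3, details column | Comment attached to a listed row | No row to attach it to |
| SAE recording (synopsis, glossary, 5.1) | Serious events | Only if serious |
| *C. difficile* diarrhoea, related readmissions (2.3) | Those events | No |
| Changes to antibiotic therapy (3.9) | That a change occurred | No reason is asked for |
| Appendix 4, reasons for missed doses | Side effects as a reason for missing doses | Not the reaction itself, and only if doses were missed |

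No named route covers it. Equally, no text says that only Appendix 3 rows count.

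**2. Figures in the plan.** The protocol gives no antibiotic reaction rate and no precision target for this outcome. Its one precision figure, an interval under 20% with 120 participants (6.1), is for feasibility outcomes. It reproduces as a full width at 50%: 2 × 1.96 × √(0.25/120) = 17.9 points. It does not bear on this point.

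**3. Effect of missed participants.** Let p6 and p2 be the true risks in the 6-week and 2-week arms, and s6 and s2 the shares of affected participants who are recorded. With no false positives:

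observed difference = s6·p6 − s2·p2 = (p6 − p2) − [(1 − s6)·p6 − (1 − s2)·p2].

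The observed difference therefore changes by the gap between arms in the absolute percentage missed. Only participants whose reactions are all unlisted are missed.

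*Equal shares (s6 = s2 = s):* observed difference = s(p6 − p2), with 95% half-width 1.96 × √[s·p6(1 − s·p6)/60 + s·p2(1 − s·p2)/60]. The risks and shares below are assumptions. Differences are 6-week minus 2-week, in points, with half-width:

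| s | 20% v 10% | 30% v 15% | 40% v 20% |
|---|---|---|---|
| 1.0 | 10.0 ± 12.7 | 15.0 ± 14.7 | 20.0 ± 16.0 |
| 0.9 | 9.0 ± 12.1 | 13.5 ± 14.2 | 18.0 ± 15.6 |
| 0.8 | 8.0 ± 11.5 | 12.0 ± 13.6 | 16.0 ± 15.0 |
| 0.7 | 7.0 ± 10.9 | 10.5 ± 12.9 | 14.0 ± 14.4 |

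The arm-level rates fall by the same factor. At s = 0.8, 30% is recorded as 24% and 15% as 12%.

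*Other patterns, from 30% v 15%:*
- 5 points missed in each arm: (30 − 5) − (15 − 5) = 15.0, unchanged. The same holds for 2 points in each arm.
- 2 points missed in the 6-week arm and 5 in the 2-week arm: (30 − 2) − (15 − 5) = 18.0, wider.

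*False positives as well.* With specificity sp equal in both arms, observed difference = (s + sp − 1)(p6 − p2). For 30% v 15% and sp = 0.9, this is 13.5 at s = 1.0 and 10.5 at s = 0.8. The loss from missed events is again 3.0 points.

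**The case against.** **A reader might infer that unlisted reactions are not counted.** The text does not go that far. Section 3.9 introduces its items as what the data will include, the REDCap form is not shown, and nothing makes Appendix 3 exclusive. A participant with any listed event is still recorded. What stands is a risk of under-recording.

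**A reader might infer that the outcome is any reaction at all.** The glossary limits it to unexpected ones. If a given unlisted reaction is judged expected, its absence from the form costs the outcome nothing.

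**A reader might infer that the difference between arms must shrink, because one arm is treated three times as long.** Longer exposure does not by itself produce proportional shrinkage; an equal missed share does. Using the same form in both arms makes equal shares a reasonable default, but the documents do not establish them.

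**Nausea and vomiting may be a conventional combined label.** That is a fair reading, and the text does not exclude nausea alone. The fault is the ambiguity.

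**The missed share may be small.** Several rows use absolute thresholds without comparison to baseline (haemoglobin, platelets, bilirubin). Peripheral neuropathy is listed without qualification, in a population whose foot infection the glossary links to neuropathy. Many participants may already tick a row, so few would have only unlisted reactions. This stands, and it weakens any claim about size.

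**Conclusion.** The mismatch is visible in the protocol: an open-ended outcome within the primary endpoint, and a closed list as the only named form for its non-serious events. Unlisted non-serious reactions may go unrecorded. Missed events can only lower the recorded rate in each arm. If the missed share is equal in both arms, they also bias the risk difference towards zero.

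The size cannot be derived from the documents. For assumed risks of 30% v 15% and 10 to 30% of affected participants missed, the shift is 1.5 to 4.5 points, well inside a half-width of about 13 to 15 points. For 40% v 20% at 30% missed, the interval runs from −0.4 to 28.4 instead of 4.0 to 36.0. That needs the largest share considered, and the protocol sets no significance criterion for this outcome. The bias would nonetheless be systematic and would carry into planning figures.

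This is a cheap improvement to consider, not a defect that invalidates the safety comparison.

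**What to change.** 1. Add a final row to Appendix 3: *Other reaction attributed to the antibiotic or its delivery (specify)*. Have the free text coded without sight of allocation.
2. Reword the joint row to *Nausea and/or vomiting*, so that sites score it alike.
3. Leave the outcome as the glossary defines it, including its attribution to the antibiotic. The new row widens what is collected; the definition still decides what counts. Do not make the outcome any ticked row, because that would drop the limit to unexpected reactions and count laboratory and neuropathy rows that carry no attribution.

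The cost is one added row and one reworded row on the data collection form, plus the work of coding free text. Treatment and visits do not change.

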| Initial assessment | 
Ulcer assessment
 
 
• Ulcer location 
 
○ Ulcer onset (approximate date of onset)
 
○ Precipitant of ulcer (trauma, pressure injury, iatrogenic, etc)
 
○ Recurrent ulcer (yes/no)
 
○ Ulcer measurement (maximum diameter and perpendicular diameter, mm)
 
○ Ulcer depth (mm)
 
 
 
 
Wifl score
 
 
• Depth grade 
 
○ Ischaemia grade
 
○ Infection grade
 
 
 
 
Systemic antibiotic therapy within last 30 days
 
 
• Duration of antibiotic therapy 
 
○ Antibiotic used
 
 
 
 
Microbiology results
 
 
• Wound swab collection (yes/no) 
 
○ Date of wound swab
 
○ Organisms identified
 
 
 
 
Serum biomarkers
 
 
• Baseline C-reactive protein (mg/L)
 
• Baseline peripheral white cell count (<math>\times 10^9/L</math>)
 
 |

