|                         | Thrombocytopenia: platelet count <150 *10  /L                                                                                                                                                                                                                                |                            |         |
| Hepatobiliary    | Cholestasis: total bilirubin >21µmol/L                                                                                                                                                                                                                                                   |                            |         |
|                         | Transaminitis: AST or ALT >3 times patient's baseline                                                                                                                                                                                                                                    |                            |         |
| Renal            | Increase in serum creatinine >1.5 times patient's baseline                                                                                                                                                                                                                               |                            |         |
| Neurologic       | Altered mental status compared to patient's baseline                                                                                                                                                                                                                                     |                            |         |
|                         | Peripheral neuropathy                                                                                                                                                                                                                                                                    |                            |         |
|                         | Seizures                                                                                                                                                                                                                                                                                 |                            |         |

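### Appendix 3 scores laboratory adverse events on blood values the protocol does not name for measurement, and two of them against a baseline it does not collect

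*Protocol*

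**What the plan says.** Section 2.3 of the protocol states "The primary endpoint will be feasibility and safety of the trial" and lists "Antibiotic-associated adverse event" among the safety outcomes. The glossary illustrates that term with "allergic reaction, end-organ toxic effect, gastrointestinal intolerance, haematological abnormalities, etc", so laboratory toxicity is meant to count. Section 6.2 reports safety as a risk difference with a 95% confidence interval.

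Section 3.9 collects medication-related adverse events at days 14, 42 and 90 with the Appendix 3 form. Its laboratory items include "Anaemia: Hb<100g/L", which is an absolute cut-off, and "Transaminitis: AST or ALT >3 times patient's baseline" and "Increase in serum creatinine >1.5 times patient's baseline", which are ratios. Each item is answered yes or no, with a free column for details.

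The follow-up bloods in section 3.9 are given as "Serum biomarkers (total peripheral white cell count, serum C-reactive protein"), and section 3.7 gives the same two at baseline. Appendix 2 has "Baseline C-reactive protein (mg/L") and the white cell count as its biomarker fields; HbA1c is the only other blood chemistry value. Appendix 1 marks blood tests at days 0, 14 and 42 without saying which.

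**The concern.** An event definition can be applied only if the value it uses is measured. Where Appendix 3 uses a value that no visit is told to measure, the item can be scored only when the treating clinician happens to order the test. Two consequences follow.

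First, toxicity can be missed. The form has no way to say that a test was not done, so an untested participant may be entered as not having the event.

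Second, ascertainment may differ by arm. Planned treatment lasts 2 weeks in one arm and 6 in the other, no blinding of treatment is described, agent and route are left to clinicians (section 3.6), and visits may be remote (section 3.5). Reasons for ordering bloods need not be the same in the two arms.

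A separate problem affects the ratio events. Without a baseline AST, ALT or creatinine the ratio cannot be formed, and no analysis plan can recover a baseline that was never drawn. The pilot is also meant to supply estimates for later trials (section 6.1), so the gap would carry forward.

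**Working it through.** The plan states no figure here, so the check is a match of each Appendix 3 laboratory event against every place that names a blood test (sections 3.5, 3.7 and 3.9, Appendices 1 and 2).

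| Event | Value needed | Named at baseline | Named at follow-up | Type |
|---|---|---|---|---|
| Leukopenia | white cell count | yes | yes | absolute |
| Anaemia | haemoglobin | no | no | absolute |
| Thrombocytopenia | platelets | no | no | absolute |
| Cholestasis | bilirubin | no | no | absolute |
| Transaminitis | AST or ALT | no | no | ratio to baseline |
| Creatinine rise | creatinine | no | no | ratio to baseline |

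Counts:
- Events defined: 6. Value named: 1. Value not named: 6 − 1 = 5.
- Of those 5, haemoglobin and platelets (2) normally come with the blood count that yields the white cell count. For them the gap is a missing field, not a missing sample.
- With no named source at all: 5 − 2 = 3 (bilirubin, AST/ALT, creatinine).
- Events that need a baseline: 2. Baselines collected for them: 0.

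Even leukopenia is unclear at day 90: section 3.9 lists biomarkers for all three follow-up visits, while Appendix 1 marks no blood test at day 90. Section 3.5 also places the second repeat sample at day 45, where the other sections have day 42.

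Can the bias between arms be sized? Suppose a share p of participants chronically meets an absolute cut-off, with no drug effect, and shares t2 and t6 are tested after day 14 in the 2-week and 6-week arms. The recorded difference is p × (t6 − t2). If a share q has already been tested by day 14, independently of later testing and equally in both arms, it becomes p × (1 − q) × (t6 − t2). All inputs are assumptions; the documents give none.
- p = 10%, 20%, 30%; t2 = 30%, t6 = 70%; q = 0: 0.1, 0.2, 0.3 × 0.4 = 4, 8, 12 points.
- Same, q = 0.5: 2, 4, 6 points.
- Same, q = 1: 0 points.
- t2 = 70%, t6 = 30%, q = 0: −4, −8, −12 points.

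Size and sign are set by the assumptions. The formula also does not apply to the two ratio events, because a stable chronic abnormality does not exceed a multiple of itself. Among the three analytes with no named source it fits only bilirubin.

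**The case against.** The strongest reply is that the blood-test row in Appendix 1 may be intended to cover renal and liver panels, and that a full blood count supplies haemoglobin and platelets anyway. The second half stands: those two are a recording gap. A reader might infer from the table that five of the six events rest on tests never scheduled, and the documents do not support that. The first half does not close the gap. The row is unspecified, and each section that does specify the biomarkers gives only white cell count and C-reactive protein.

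A baseline could be taken from the medical record. That is possible, but no source or time window is given.

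The glossary requires a reaction to a prescribed antibiotic, so long-standing anaemia should not count, and the details column could record this. Serious toxicity is also captured as serious adverse events, which are adjudicated blind (section 5.1). This limits the harm. But the laboratory items carry no condition of attribution or new onset, whereas the diarrhoea and nausea items do. Without a day 0 value, new and old cannot be told apart.

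A reader might also infer that the 6-week arm will be tested more, and that the comparison is therefore tilted towards the short course. No passage says so. Suspected recurrence, or antibiotics continued past plan, could equally prompt bloods in the 2-week arm. That untested participants will be recorded as event-free is likewise a risk created by the form, not a stated rule; section 6.2 says missing data will be explored.

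**Conclusion.** The point holds as an internal mismatch. Three of six laboratory events use values not named at any visit, two more have no recording field, and both ratio events lack their baseline. This affects one component of a safety outcome within the primary endpoint, and it would not invalidate the trial.

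The counts rest only on the text, together with the ordinary expectation that haemoglobin and platelets accompany a white cell count. That toxicity can be missed follows directly when no test is done. That ascertainment could differ by arm is a reasoned risk in an open comparison of 2 with 6 weeks. Its size and direction are not derivable, and no point estimate of bias should be attached to it. The matter should be settled in the protocol, because the visit schedule and data fields determine what any later analysis plan has to work with.

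**What to change.** In sections 3.7 and 3.9 and Appendices 1 and 2, record haemoglobin and platelets from the blood count already taken, and add creatinine, bilirubin and AST/ALT to the draws at days 0, 14 and 42, identically in both arms. Reconcile the day 42/45 and day 90 blood-test entries at the same time.

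In Appendix 3, add a not-tested response to each laboratory item and define the baseline as the recorded day 0 value, so that pre-existing abnormalities can be separated from new ones. Day 0 is not necessarily free of antibiotics, since section 4.3 permits up to 7 days of prior therapy, but it is the same reference point in both arms.

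Keep events found on unscheduled tests in the safety outcome, flag their source, and add a sensitivity analysis restricted to scheduled samples. Making that restriction the main analysis would drop toxicity that appears and resolves between days 14 and 42, when only the 6-week arm has planned antibiotics.

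Cost: a protocol and CRF amendment and a small laboratory charge for three panels per participant, with no extra visit or venepuncture.

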### 3.7 Baseline participant data

Participants will have the following baseline data collected (see Appendix 2):

- Age
- Sex
- Charlson Comorbidity Index
- HbA1c level within last 90 days

- e. Ankle-brachial pressure index and/or systolic toe pressure measurement
- f. Ulcer location
- g. Ulcer size
- h. Ulcer classification score (Wlfl)
- i. Antibiotic therapy prior to randomisation
- j. Serum biomarkers (total peripheral white cell count, serum C-reactive protein)
- k. Results of baseline wound swab for bacterial culture

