## Appendix 1 – Schedule of events

|                            | Day 0 | Day 14 | Day 42 | Day 90 |
|----------------------------|--------------|---------------|---------------|---------------|
| Baseline data       | X            |               |               |               |
| Ulcer assessment    | x            | x             | x             | X             |
| X-ray               | x            | x             | X             |               |
| Blood tests         | x            | x             | x             |               |
| Outcome assessments |              | x             | x             | x             |

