| Dermatologic     | Rash                                                                                                                                                                                                                                                                                     |                            |         |
|                         | Red-man syndrome                                                                                                                                                                                                                                                                         |                            |         |
| Cardiac          | QTc prolongation (>400ms in males or >460ms in females) on ≥2 ECG tracings                                                                                                                                                                                                               |                            |         |
| Anaphylaxis      | Generalised, rapidly progressing, multi-system IgE-mediated allergic reaction (symptoms include difficult or noisy breathing, swelling of the tongue, swelling or tightness in throat, difficulty talking or hoarse voice, wheeze or persistent cough, persistent dizziness or collapse) |                            |         |

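### Appendix 3 sets the QTc adverse-event cut-off 60 ms lower for men than for women without explanation, and the row has no baseline or attribution clause

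*Protocol*

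**What the plan says.** The Cardiac row of Appendix 3 reads "QTc prolongation (>400ms in males or >460ms in females) on ≥2 ECG tracings". Both figures are absolute levels, and no source is cited.

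Section 3.9 lists "Medication-related adverse events (see Appendix 3") among the data collected at days 14, 42 and 90. Section 2.3 makes feasibility and safety the primary endpoint and names "Antibiotic-associated adverse event" as a safety outcome. Section 6.2 reports safety as a risk difference with a 95% confidence interval. The glossary defines this outcome as an unexpected adverse reaction to an antibiotic that was prescribed, so it requires a link to the drug.

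Other rows of Appendix 3 build in a comparison or a link. Creatinine is defined as "Increase in serum creatinine >1.5 times patient's baseline" and transaminases as "Transaminitis: AST or ALT >3 times patient's baseline". Nausea and vomiting must be "associated with antibiotic administration, in the absence of alternate explanation", and the diarrhoea row has a similar condition. The QTc row has neither.

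No ECG appears in the baseline list (Section 3.7), the follow-up list (Section 3.9), Appendix 1 or Appendix 2.

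**The concern.** Two sex-specific limits for the same measurement, printed in one line, would normally sit close together. A 60 ms gap with no stated reason suggests that a digit in the male figure is wrong. If the figure is used as printed, the form could record QTc prolongation in men whose QTc no drug has changed.

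The row also cannot separate a long-standing QTc value from a reaction to the antibiotic. It does not refer to an earlier ECG, the protocol collects none, and the row does not ask for attribution. At stake is the accuracy of one row of the form that records medication adverse events for the safety half of the primary endpoint.

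**Working it through.** **1. What can be reproduced.** The cut-offs are definitions with no derivation, so there is no stated figure to reproduce. The check asks what the printed male cut-off implies.

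**2. Inputs.**
- From Appendix 3: more than 400 ms (men), more than 460 ms (women), on at least two tracings.
- From Section 6.1: 120 participants.
- Assumed, because the protocol gives none of these: QTc is normal; male mean 390-420 ms (380 ms as a lower extreme); SD 20 ms (range 15-25); correlation between two tracings in one man 0.8 (range 0.5-0.9); 65% men; share of men with two ECGs from 0 to 100%.

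**3. How large the gap is.** If women's true mean is *d* ms above men's, the unexplained part of the gap in SD units is (60 − *d*)/SD. The extremes for *d* = 0-20 and SD 15-25 are:
- (60 − 0)/15 = 4.0
- (60 − 20)/25 = 1.6

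A sex difference of up to 20 ms therefore leaves 1.6 to 4.0 SD unexplained.

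**4. Share of unaffected men who meet the rule.** The rule needs two tracings, so the relevant quantity is P(both > c). This is the bivariate normal probability that two standard normal variables with the given correlation both exceed (c − mean)/SD. With SD 20 and correlation 0.8:

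| Male mean (ms) | One tracing > 400 | Both > 400 | Both > 460 |
|---|---|---|---|
| 380 | 16% | 10% | 0.0% |
| 390 | 31% | 22% | 0.0% |
| 400 | 50% | 40% | 0.0% |
| 410 | 69% | 60% | 0.2% |
| 420 | 84% | 78% | 1.0% |

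For means of 390-420 the two-tracing share is 22-78%. Over the full grid (means 380-420, SD 15-25, correlation 0.5-0.9) the share above 400 ms runs from about 3% to 88%. The share above 460 ms runs from 0% to 3% (same means and SDs, correlation 0.8). The second tracing lowers the share but does not remove the problem, because tracings from the same man are correlated.

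**5. How many men.** Expected number = 120 × 0.65 × (share of men with two ECGs) × P(both > 400), for means 390-420, SD 20 and correlation 0.8:
- No ECGs taken: 0
- 5% of men: 78 × 0.05 × (0.219 to 0.780) = 0.9 to 3.0
- 10% of men: 78 × 0.10 × (0.219 to 0.780) = 1.7 to 6.1
- All men: 78 × (0.219 to 0.780) = 17 to 61

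The last line is only an upper bound, since no ECG is scheduled.

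**6. The row against the glossary.** The glossary requires a reaction to the antibiotic. The QTc row asks only whether a level was exceeded. The two do not agree, and the protocol does not say which one decides whether an event is counted.

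**The case against.** The strongest reply is that the practical effect is small and perhaps nil. Several parts of it stand.

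- **Number of men.** A reader might infer that many unaffected men in the trial would be labelled. The protocol does not support that. A man can meet the rule only if at least two ECGs happen to be taken, and none is planned. The high percentages apply only to men who have two tracings.
- **Direction of bias.** A reader might also infer that six weeks of antibiotics brings more ECGs than two, so that false events would favour the short course. Nothing in the protocol shows this. Both arms are followed for 90 days and the agent is the clinician's choice. ECGs could cluster at the start of treatment, which both arms share, or at readmission or retreatment, which might be commoner after the short course. With equal ECG use there is no expected spurious difference.
- **Counting.** A positive tick on the form is not stated to be an outcome event, and the glossary would let an investigator discount it. But the QTc row does not say so, and the blinded adjudication in Section 5.1 covers only serious adverse events.
- **Other rows.** Haemoglobin, white cell count, platelets and bilirubin are also absolute levels, so the missing baseline comparison is not peculiar to QTc.
- **Weight.** QTc is one of 15 rows, feeding one of four safety outcomes, in a pilot with no stated decision threshold.

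None of this explains the 60 ms gap.

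**Conclusion.** The point holds as a minor one. The two cut-offs in the QTc row differ by 60 ms without a stated reason, and an error in the male figure is the likeliest explanation. That is an inference from the line itself, and only the source can settle it.

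The percentages in the check rest wholly on assumed QTc distributions. They show how unselective the male limit would be among men with two tracings. They do not predict event counts, and the protocol supports no estimate of a between-arm difference. The mismatch between the row and the glossary needs no assumption: it can be read directly from the text.

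**What to change.** 1. Check the male cut-off against the source from which the row was taken, and correct it in Appendix 3 and the matching CRF field. No replacement value is proposed here.
2. Reconcile the row with the glossary: a QTc value counts as an antibiotic-associated adverse event only if it is judged attributable to the antibiotic, using an earlier ECG where one exists.
3. Otherwise, record the QTc value without counting it automatically. Keeping the measured value on the form lets entries be reclassified once the cut-off is settled.

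The cost is one line of Appendix 3 and one CRF field. The downside is that fewer QTc events will be counted. Because the protocol collects no baseline ECG, some of those left out may be genuine, so uncounted values should still be listed. The change does not even out who happens to have an ECG, and that limitation should be stated when the outcome is reported.
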